### Control

We have chosen to use a treatment as usual (TAU) control condition, as this provides a fair comparison with routine practice by vocational advisers, and will answer the question of whether use of the DA in addition to current standard practice is superior to standard practice alone. Employment advisers often discuss disclosure needs with those clients seeking competitive employment, so that TAU will in many cases include an unstructured discussion of some of the content covered by the DA. Some vocational advisers using the supported employment model encourage disclosure as part of the process of obtaining work. However, advisers do not routinely provide information about discrimination following disclosure and employees’ rights; instead they do so in response to questions from a client. More broadly, TAU consists of an initial assessment of work history, qualifications, employment and career goals and clinical information. Advisers then assist with augmenting job seeking skills, finding training courses and voluntary placements and providing follow up to those in work. Support for people in work includes helping with requests for workplace adjustments when the need for these arises.

### Objectives

The aims are to determine whether a full scale RCT of the CORAL decision aid tool is justifiable and feasible and to optimise its design
[15,16]. Specific objectives are to (i) establish parameters of a future trial, by examining the effect of the DA on decisional conflict regarding disclosure both immediately and at 3 months post first use and determining the optimal primary outcome for a full scale trial from a range of employment related measures; (ii) optimise the evaluation, by testing study procedures, including: the sample that can be recruited and retained using the inclusion and exclusion criteria; the resource implications in terms of full time equivalent needed for research assistants to recruit sufficient numbers and carry out the study procedures in the time available; whether the batch of measures is acceptable vs. leads to too much respondent burden; the use of a questionnaire on employment and disclosure related activities; the randomisation method, in this case individual level randomisation, including the methods for avoiding and measuring contamination; recruitment and retention methods for service users and vocational counsellors; the choice of measures for a full scale trial based on results of qualitative interviews with participants; (iii) optimise the intervention, by collecting feedback on the DA form a larger sample than was used in the previous pilot.

### Hypotheses

While we shall conduct hypothesis testing this is not the main objective of the study, as this is the purpose of the future large scale trial. The reporting of this study will not therefore emphasize the results of hypothesis testing over the reporting of whether the objectives were met
[17]. Our hypotheses are derived from the conceptual model in Figure
2 and fall into three groups. Regarding the effect of the intervention, we expect that, regardless of what the disclosure decision is, having a lower level of decisional conflict and being at a later stage of decision will allow the participant to take action regarding seeking work, resulting in a greater level of empowerment and a reduction in behavioural withdrawal. Thus, compared to the control group, those in the intervention group will show at 3 months
[1]: lower decisional conflict regarding disclosure
[2]; a later stage of decision making regarding disclosure
[3]; higher frequencies of work related actions
[4]; a higher level of empowerment
[5] lower frequencies of withdrawal as a response to stigma (in any context rather than just employment). The model shown in Figure
2 will be investigated using process evaluation and qualitative data collection to identify the most robust associations to carry forward into a final modified and simplified version of the model to be used in the subsequent full scale RCT. 

**Figure 2 F2:**
[figure not shown]
Mechanisms of DA intervention.

The DA is not designed either to cause an increase or decrease in rates of disclosure to an actual or potential employer but may have either effect. It may increase disclosure through increasing knowledge about being able to request workplace adjustments. On the other hand, knowing that there is a choice that can be made regarding disclosure may make some people feel more confident about not disclosing. We will therefore study the relationship between use of the DA and subsequent disclosure and use qualitative methods to explore any apparent effect or lack thereof.

### Primary outcome measures

#### Decisional conflict

The decisional conflict scale measures personal perceptions of: uncertainty in choosing between options; modifiable factors contributing to uncertainty including feeling uninformed, lack of clarity about personal values and feeling unsupported in decision making; and effective decision making such as feeling the choice is informed, values-based, likely to be implemented and expressing satisfaction with the choice. The 16 item version of the scale is the most commonly used
[18]. A total score and 5 sub-scores (uncertainty; informed; values clarity; support and effective decision) are generated. Scores exceeding 37.5/100 are associated with decisional delay or feeling unsure about implementation.

#### Stage of decision making

The stage of decision making scale measures the individual’s readiness to engage in decision making
[19]. It consists of 1 item with 6 response options anchored at 1 (haven’t started to think about the choices) and 6 (have already made a decision and am unlikely to change my mind).

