**Methods:**

In this single blind exploratory RCT in London, a total of 80 participants (inclusion criteria: age ≥18 years, on the caseload of a specialist employment adviser working with people with mental illness; referred to the adviser either from primary care via Improving Access to Psychological Therapies or secondary mental health service; currently seeking or interested in either paid or voluntary employment, and a Decisional Conflict Scale score of 37.5 or greater and stage of decision score 1–5) will be recruited from vocational advice services. After completing a baseline assessment, participants will be randomly assigned to one of two conditions (1) Use of the CORAL Decision Aid (DA) in addition to treatment as usual or (2) Treatment as usual. Those allocated to the DA condition will be given it to read and complete, and the researcher will be present to record the time taken and any content that causes confusion. Intervention participants may keep the decision aid but are discouraged from showing it to other service users to avoid contamination. Follow up interviews will be conducted at 3 months. Primary outcomes are: (i) stage of decision making score; (ii) decisional conflict scores and (iii) employment related outcomes. Secondary analyses will identify predictors of disclosure and qualitative analysis will explore the impact of the intervention.

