### Participants

Eligible service users will (i) be on the caseload of a specialist employment adviser working with people with mental illness; (ii) have been referred to the adviser either from the primary care based mental health service Improving Access to Psychological Therapies (IAPT) or secondary mental health care service; (iii) be aged 18 years or older; (iv) be currently seeking either paid or voluntary employment or interested in seeking paid or voluntary employment (v) have a Decisional Conflict Scale score of 37.5 or greater (showing at least moderate decisional conflict) and a Stage of Decision Scale score of 1–5 (showing the decision has not yet been reached); and (vi) give written, informed consent. We will exclude service users who have insufficient literacy in English to use the DA or who lack capacity to provide informed consent. Figure
1 shows the CONSORT flow chart for participants.

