### Analysis plan

The principal analysis of effectiveness will compare the primary and secondary outcome measures at 3 months. Changes in Decisional Conflict Scale scores are not prone to cut-off limits and are expected to be normally distributed. For both this and other normally distributed continuous outcome measures, an independent two sample t-test will be used to compare the change in effects (T1-T0) for the two groups (control and intervention). When continuous variables are predicted to be skewed (e.g. number of disclosures made), these can be tested using a two-sample Wilcoxon rank-sum test. The differences in number of disclosures made (T1-T0) for the two groups (control and intervention) can be compared. While items such as job offers and disclosure will be too infrequent to provide reliable comparisons, others such as appointments kept with the vocational adviser and submitted applications will be used as proxy measures for future employment outcomes. We will use confidence intervals for the effect sizes for these employment related activities to judge whether a full scale trial is indicated.

Attendance and dropout rates can be compared in terms of their baseline characteristics to see whether there are any obvious differences between retained and dropout participants. Adjustments to these analyses will be made to compensate for multiple testing. To study factors predicted by our model (see Figure
2) to be associated with disclosure we will use logistic regression. Each instrument will be studied to see whether it performs well enough for inclusion in a future trial. A correlation matrix will be formed from the items to calculate internal consistency and reliability, and to assess the appropriateness of forming composite or summary scores for previously defined sub-scales. Along with the histograms of each subscale, the data allow assessment of the appropriateness (particularly ceiling and floor effects) of the measures. Variables that perform well (and that appear not to be measuring the same thing) will be included in the logistic regression model, while adjusting for gender and diagnosis as these have been found to be associated with disclosure in other studies
[28,29].

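### Stage of decision, a six-level ordinal primary outcome, has only unadjusted tests meant for continuous data on offer; analysed as change it would lose power and miss the stated hypothesis

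*Protocol article*

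**What the plan says.** The abstract of the protocol article lists the item first among the primary outcomes: "Primary outcomes are: (i) stage of decision making score; (ii) decisional conflict scores and (iii) employment related outcomes". The section on stage of decision making describes the scale: "It consists of 1 item with 6 response options anchored at 1" (thinking about the choices not yet begun), with 6 meaning a decision made and unlikely to change. Under Participants, eligibility requires "a Stage of Decision Scale score of 1–5", which the protocol reads as a decision not yet reached.

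The Analysis plan opens by saying that primary and secondary outcomes will be compared at 3 months. It then gives two tests:

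- For the Decisional Conflict Scale and other normally distributed continuous measures, "an independent two sample t-test will be used to compare the change in effects (T1-T0) for the two groups".
- "When continuous variables are predicted to be skewed (e.g. number of disclosures made), these can be tested using a two-sample Wilcoxon rank-sum test". The sentence that follows applies this to T1-T0 differences in the number of disclosures.

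The t-test is justified for one scale only: "Changes in Decisional Conflict Scale scores are not prone to cut-off limits and are expected to be normally distributed". Logistic regression is kept for predictors of disclosure. Ceiling and floor effects are to be examined when the instruments are appraised, with no link to the choice of test. Stage of decision is not assigned to either test, and no ordinal or baseline-adjusted comparison is named.

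**The concern.** The item is neither normally distributed nor continuous, so neither route fits it as described. The one worked-out quantity in the plan is T1-T0 change, and an analyst following the text could well use it here. Three things would then go wrong.

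- **Scoring.** A move from 1 to 2 counts the same as a move from 5 to 6, although only 6 is a settled decision. Ranking the differences does not cure this, because both moves are a difference of 1.
- **Target.** The Hypotheses section predicts that the intervention group will be at a later stage at 3 months. That concerns the stage reached, not the number of steps moved. The steps available depend on entry level: 6 minus baseline, so 1 for someone entering at 5 and 5 for someone entering at 1.
- **Efficiency.** Baseline stage is collected on everyone as an eligibility measure, and neither test conditions on it.

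The trial is meant to set parameters and choose measures for a full-scale trial. A compressed mean change that is hard to interpret could lead to this measure being discounted wrongly.

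**Working it through.** **1. The plan's own figure.** Sample size section: change 16.5 in the intervention group, 4 under usual care, SD 17.5. The effect size is (16.5 − 4)/17.5 = 12.5/17.5 = 0.714, stated as 0.71. For 80% power at two-sided 5%, the normal approximation gives 31 (0.714) or 32 (0.71) per group. The stated 32 is reproduced. It covers the Decisional Conflict Scale only; no power is claimed for stage of decision.

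**2. Inputs that must be assumed.** The documents give no baseline distribution of stage, no baseline-to-follow-up correlation (ρ) and no expected effect on this item.

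**3. Change score against baseline adjustment, with no ceiling and no categories.** Take a normal outcome with SD 1 at both times, shift 0.6 and n = 35 per arm.

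- Change: SD = √(2(1 − ρ)).
- Baseline-adjusted: SD = √(1 − ρ²).
- Noncentrality = (0.6/SD) × √(35/2); power from the noncentral t, two-sided 5%.

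| ρ | SD, change | Power, change | SD, adjusted | Power, adjusted | Gap (points) |
|---|---|---|---|---|---|
| 0.3 | 1.183 | 55% | 0.954 | 74% | 18 |
| 0.5 | 1.000 | 70% | 0.866 | 82% | 12 |
| 0.7 | 0.775 | 89% | 0.714 | 93% | 4 |

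Gaps are taken before rounding. A sizeable loss arises with no ceiling at all.

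**4. Six categories, entry capped at 5.** Simulation of a latent normal cut into six stages, baseline restricted to 1–5, 32 per arm, latent shift 0.71 SD, general drift 0.3 SD, 2000 runs per setting. Cells show power for t-test on change / rank-sum on change / rank ANCOVA on the 3-month stage.

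| Share entering at stage 5 | ρ = 0.3 | ρ = 0.5 | ρ = 0.7 |
|---|---|---|---|
| 9% | 68/68/79% | 80/80/84% | 91/91/93% |
| 20% | 61/59/78% | 73/72/84% | 89/88/93% |
| 40% | 49/46/74% | 62/61/81% | 82/80/92% |

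The change-score tests have less power in all nine settings. The smallest loss is 92.5 − 91.4 = about 1 point (t-test, 9%, ρ = 0.7). The largest is 74.3 − 45.9 = about 28 points (rank-sum on change, 40%, ρ = 0.3). At ρ = 0.5 the t-test loses about 5, 10 and 19 points as the share entering at stage 5 rises through 9%, 20% and 40%. A proportional-odds model (300 runs) shows the same pattern: for 20% at stage 5 and ρ = 0.5, 85% against 74% for the t-test on change.

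**5. How much is the ceiling?** With 35 per arm, shift 0.6 SD and drift 0.3 SD, the t-test on change has 54/67/85% power at ρ = 0.3/0.5/0.7, against 68/76/88% for a baseline-adjusted rank analysis: gaps of 14/9/3 points. With the ceiling removed the gaps are 13/9/3. Here the ceiling adds about one point at most.

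**6. Validity.** With no true effect, the t-test and rank-sum test on change reject in about 4 to 6% of runs in the step 4 settings.

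**The case against.** The strongest reply is that the plan never assigns this item to a change-score test. Its first sentence speaks of comparison at 3 months, the t-test is limited to normally distributed continuous measures, and the rank-sum sentence is permissive and refers to change only through the disclosure example. A rank-sum test on the 3-month stage would be valid for ordinal data and would match the hypothesis. On this view all that is missing is a detail that a condensed article may leave to the full plan.

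Much of this stands. A reader might infer that this primary outcome will be analysed as T1-T0 change; the documents do not say so, and the point is therefore conditional. But the article does prescribe tests, and both are unadjusted. In the simulation of step 4, even the favourable choice, a rank-sum test on the 3-month stage, falls short of rank ANCOVA: by about 1 point (73.0% against 74.3%; 40% at stage 5, ρ = 0.3) and up to about 12 points (80.6% against 92.5%; 9% at stage 5, ρ = 0.7). Naming a better method for data already collected is more than filling in a detail.

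A reader might also infer that power is lost chiefly because scores hit the ceiling at 6. Steps 3 and 5 do not support that as the general mechanism: most of the gap appears without any ceiling. It becomes material only if many enter near stage 5, and the documents do not say how many will.

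Two further replies stand. Type I error is not harmed. The Hypotheses section also says that hypothesis testing is not the main objective, and the planned check for ceiling and floor effects would reveal a problem with the item before a full trial.

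**Conclusion.** The point holds in conditional form. A six-level ordinal primary outcome is left with two unadjusted tests described for continuous data, and is assigned to neither. If T1-T0 change is used, the analysis equates unequal steps, does not address stage at 3 months, and loses power by not conditioning on baseline.

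The loss runs from about 1 to 28 percentage points over the settings examined. It is smallest with high correlation and low entry stages, and largest with low correlation and many entering near stage 5. All of these figures rest on assumed shift, drift, correlation and baseline distribution. No stated power is missed, since power is claimed only for the Decisional Conflict Scale. Severity is minor to moderate: the issue is efficiency and interpretation, in a trial where testing is secondary.

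**What to change.** State in the Analysis plan that stage of decision will be compared between arms at 3 months, adjusted for baseline stage, by proportional-odds regression with sparse categories collapsed where needed, or by rank ANCOVA if proportional odds is doubtful. Report the effect with its 95% confidence interval (the common odds ratio for the proportional-odds model) and the percentage at stage 6 in each arm. State that T1-T0 change will not be used for this item.

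The cost is a change of wording; no new data are needed. The small downside is the proportional-odds assumption, which is hard to check with some 32 to 35 participants per arm.

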#### Employment related outcomes

We will administer a questionnaire to assess the occurrence and frequency of employment related activity and disclosures made to employers. The baseline interviews will be used to pilot this questionnaire. Its content will cover the previous 3 months regarding: appointments made and kept with the vocational counsellor; applications submitted; interviews attended; jobs offered and accepted; verbal disclosure and its timing e.g. at interview, post offer, after starting employment; written disclosure and its timing e.g. on application forms or occupational health forms; requests for workplace adjustments and the outcome of such requests; job loss and reason for loss; other employment related activity such as training e.g. on CV completion; non-competitive employment and volunteering; and income or job title. We will measure employment rates pre- and post-intervention in each group. We will ask about income from employment; if people are reluctant to disclose this we will assume salary levels based on the job titles and these salary levels will be used to reflect productivity gains. The eight item short version of Work Limitations Questionnaire
[20] will also be included for participants to self-assess work performance and these data will be used to make estimates of productivity costs through work limitations whilst at work.

### Secondary outcome measures

#### Empowerment

The Boston University Empowerment Scale (BUES) 17-item version consisting of the self-esteem-self-efficacy and power-powerlessness subscales of the original 28 item scale used in a recent validation study
[21].

#### Withdrawal

We shall use the 9 item withdrawal scale of the Stigma Coping Orientation scales
[22].

### Predictors of intention to disclose: behaviour beliefs

#### Experienced discrimination

The Discrimination and Stigma Scale [3,13] is a 35 item, interview-based scale. It contains a global scale and 4 subscales: 1) Unfair treatment; 2) Stopping self; 3) Overcoming stigma and 4) Positive treatment. We will use the 22 item Unfair treatment subscale only, which has 21 specific items and one item where other experiences can be recorded.

#### Anticipated discrimination

The Questionnaire on Anticipated Discrimination (QUAD) (
http://www.sapphire.iop.kcl.ac.uk) is a self-complete measure with 14 items which address ‘areas of anticipated discrimination’. It asks participants to provide a rating of whether they expect to be treated unfairly in various areas of life.

#### Self-stigma

The Internalised Stigma of Mental Illness Scale (ISMI) is a 29-item measure that assesses mental health service users’ experience of internalised stigma. It is composed of 5 sub-scales: Alienation, Stereotype Endorsement, Perceived Discrimination, Social Withdrawal and Stigma Resistance
[21].

### Normative beliefs

#### Perceived stigma

The Perceived Devaluation and Discrimination Scale (PDD) is a 12-item, uni-dimensional, scale which measures the extent to which a person believes that most people will devalue or discriminate against someone with a mental illness
[23,24];.

### Control beliefs

#### Empowerment

The 17 item BUES will be used as above.

#### Coping orientation

Link et al. devised 5 short coping scales with a total of 20 items (the Stigma Coping Orientation Scales) to assess various approaches to coping with the stigma associated with mental illness. Five different coping orientations are assessed: secrecy, withdrawal, educating, challenging and distancing
[22,25]. More general coping orientation will be assessed using the revised Ways of Coping Questionnaire (WCQ), a self-report instrument which asks participants to think about a recent stressor and rate the extent to which they used each of 24 behaviours to cope with it
[26]. A revised factor structure for the scale, as used with people with a diagnosis of schizophrenia, has been proposed and will be used
[27].

### Qualitative data collection

#### Intervention group participants

Interviews will be conducted with up to 15 participants after outcome measures have been administered. This will explore the perceived impact of using the decision aid with respect to (i) actual and intended disclosure; (ii) job seeking behaviour and (iii) other behaviour e.g. disclosure to others. We shall also enquire about experiences over the follow up period which have modified or reinforced intentions regarding disclosure or actual disclosure. Interviews will be recorded and transcribed.

#### Control group participants

Interviews will be conducted with up to 6 consenting participants after outcome measures have been administered. This will explore actual and intended disclosure in relation to employment and others. While this was a focus of previous qualitative work with service users there have been subsequent changes both in relevant legislation (the introduction of the Equality Act 2010) and in the job market, which has contracted. Both of these factors may have influenced disclosure intentions and behaviours.

